## Background

Both smoking and depression are leading causes of disability, mortality, and morbidity worldwide [1–3]. The frequent co-occurrence of depression and smoking is well documented, and empirical work suggests that smoking-depression relations could be bi-directional [4, 5]. Epidemiological research have shown that mood disorders are more prevalent among smokers compared to nonsmokers from the general population [6–8], and it has been found that smoking is also associated with a greater risk of onset and persistence of depression [9]. In addition, among treatment-seeking smokers, several studies have found greater levels of mood disorders, in both lifetime and past-year diagnoses [10].

Evidence suggests that smokers from the general population with depressive symptoms or with a depressive disorder, compared to those without one, present higher levels of cigarette consumption, greater nicotine dependence, are more likely to suffer intense nicotine withdrawal symptoms and to fail when trying to quit smoking, have more difficulties to maintain abstinence, and have a higher risk of smoking relapse over time [5, 11–13]. Additionally, it has been shown that even very low levels of pretreatment depressive symptoms can impact smoking cessation treatment outcomes [14].

At the same time, studies conducted both in general and clinical populations have found that smoking cessation is related to mood improvement in people who are able to remain abstinent [15–17]. In a recent meta-analysis that included 26 studies assessing mental health in persons with and without psychiatric disorders, Taylor and colleagues [18] found that quitting smoking is associated with a decrease in depressive and anxiety symptoms, with a reduction in stress levels, and an improvement in quality of life.

The U.S. Preventive Services Task Force (USPSTF) found strong evidence that behavioral interventions substantially improve achievement of tobacco cessation [19]. Despite this, a reduction over time in abstinence rates has been shown following psychological and/or pharmacological smoking cessation treatment [20–22]. As recent studies suggest, this trend could be due to a change in treatment-seeking smokers, who show significantly greater self-reported depressive symptoms when compared to prior studies [20, 23].

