### Target population, blinding, randomization, and procedure

Sample selection will be carried out according to the following inclusion criteria: aged 18 or over; wishing to participate in the treatment program; providing written informed consent; and smoking 8 or more cigarettes per day. Exclusion criteria will be: a diagnosis of severe mental disorder (bipolar disorder and/or psychotic disorder); concurrent substance use disorder (alcohol, cannabis, stimulant, hallucinogen and/or opioid); having participated in the same or similar treatment over the previous year or having received pharmacological smoking cessation treatment (nicotine replacement therapy, bupropion, or varenicline) over the previous year; presence of a high life-risk pathology that would require immediate individual intervention (i.e., recent myocardial infarction); smoking tobacco products other than cigarettes (i.e., cigars); or failing to attend the first treatment session.

Two baseline assessment sessions will be carried out in a face-to-face interview. Researchers conducting such assessments will be blind to group allocation, which will occur subsequently. Due to the nature of the study, participants will be aware that they will be assigned to one of the three arms.

The randomization will be conducted according to a computer generated allocation sequence (ratio: 2.2.1.): (1) standard cognitive-behavioral smoking cessation treatment; (2) standard cognitive-behavioral smoking cessation treatment plus behavioral activation; or (3) a 3-month delayed treatment control group. After that, both active treatments will be administered in eight weekly 60-min sessions.

At the end of treatment, there will be a post-treatment assessment (during session 8) and face-to-face follow-ups at 3, 6, and 12 months (Fig. 1). Self-reported abstinence at the end of treatment and at the follow-ups will be corroborated by measures of CO in expired air. In those cases in which it is not possible to locate the participants, they will be considered to be smokers, and at the same level (in terms of tobacco-related variables) as at the baseline assessment.

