### Sample size and power analysis

Previous studies of cognitive behavioral interventions for smoking cessation [20, 33] and studies of cognitive behavioral interventions for smoking cessation with components targeting depressive symptoms [24, 31] suggest that quit rates after treatment may range between 28% and 61.9%. The sample size for this study was calculated using G*Power3 Software [34]. To detect a 20% difference between the two active groups in the proportion of individuals with tobacco abstinence after treatment, with a power of 80% and a significant *p*-value of 0.05, a total of 102 participants per active group will be required. The sample size of the delayed-treatment control group will be 51 participants. We have chosen an unbalanced design because larger abstinence rates are expected in both active groups as compared to the delayed-treatment control group.

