### Statistical analysis

All data analysis will follow the intention-to-treat principle. This conservative approach aims to minimize selection bias through the inclusion in the primary analysis of data from all the participants randomized to each group, including those who drop out of the study.

We will conduct descriptive analysis to summarize the characteristics of the total sample, and the characteristics of the participants in each of the three groups. The main analysis will be a comparison between both active groups and the control group of the proportions of abstinent smokers at the end of treatment, and between BA intervention group and standard intervention group at the end of treatment, and at 3-, 6-, and 12-month follow-ups, through chi-square tests and odds ratios with 95% confidence intervals. A *t*-test analyses will be conducted to determine whether there were any significant differences between the two active treatment groups and the control group in continuous variables such as BDI-II score. We also will conduct mediation analysis, multiple regression analysis, repeated measures ANOVA, and survival analysis.

The study results will be reported in accordance with the Consolidated Standards of Reporting Trials (CONSORT) 2010 statements [58, 59] and Standard Protocol Item: Recommendations for Interventional Trials (SPIRIT) guidelines [60, 61].

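### Minor, near-free improvement: adjust the main abstinence comparison for baseline depressive symptoms, which the protocol itself says affect quitting

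*Protocol article*

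**What the plan says.** The protocol's Statistical analysis section names a main analysis: abstinent proportions are compared between each active arm and the delayed-treatment control at the end of treatment, and between the BA and standard arms at the end of treatment and at 3, 6 and 12 months, "through chi-square tests and odds ratios with 95% confidence intervals". No covariate is attached. Regression appears only in a later sentence: "We also will conduct mediation analysis, multiple regression analysis, repeated measures ANOVA, and survival analysis". That sentence names no outcome and no covariates.

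On prognosis, the Background states that "even very low levels of pretreatment depressive symptoms can impact smoking cessation treatment outcomes", and the Discussion treats the link between depressive symptoms and difficulty in quitting as well established. The Discussion also lists enrolment regardless of current symptom level as a strength of the trial.

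On allocation, the text is "The randomization will be conducted according to a computer generated allocation sequence", with a 2:2:1 ratio and no stratification factor. According to Measures and Table 1, BDI-II, HDRS, FTCD, NDSS and the Smoking Habit Questionnaire (which includes cigarettes per day) are all collected at baseline.

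**The concern.** The trial rests on the idea that depressive symptoms make quitting harder. Because smokers enter at any symptom level, baseline BDI-II will vary across the sample. Yet neither the stated allocation nor the stated main test uses it.

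Two things follow. First, if one active arm happens to start with more depressed smokers, the crude BA-versus-standard difference shifts with that imbalance. An adjustment chosen after the imbalance is seen would be open to challenge. Second, any variation in abstinence that baseline BDI-II explains stays in the error of the crude comparison, which makes the interval wider than it need be.

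**Working it through.** **Inputs from the protocol.** Sample size and power analysis gives the target, "To detect a 20% difference between the two active groups in the proportion of individuals with tobacco abstinence after treatment", and the error rates, "with a power of 80% and a significant *p*-value of 0.05". It sets 102 per active arm and cites earlier studies in which "quit rates after treatment may range between 28% and 61.9" per cent. It does not state the reference quit rate or whether the test is two-sided.

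**Assumptions.** The 20% is an absolute difference, the test is two-sided, and the true rates are 40% versus 60% (with 28% versus 48% as an alternative). The prognostic strength of the covariates is not in the protocol, so a range is shown.

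**Step 1: reproduce the 102.** At 28% versus 48% the pooled proportion is 0.38. The uncorrected formula gives

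n = [1.96·√(2·0.38·0.62) + 0.8416·√(0.28·0.72 + 0.48·0.52)]² / 0.20² = (1.345 + 0.565)² / 0.04 ≈ 91.3.

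The continuity correction gives (91.3/4)·[1 + √(1 + 4/(91.3·0.20))]² ≈ 101.0, which rounds up to 102. Fisher's exact test at 40% versus 60% with 102 per arm has 80.1% power. The stated size therefore fits an unadjusted comparison of two proportions and needs no help from covariates.

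**Step 2: crude precision.** At 40% versus 60% the standard error of the difference is √(0.4·0.6/102 + 0.6·0.4/102) = √(0.48/102) = 0.0686. The 95% half-width is 1.96·0.0686 = 13.4 points.

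**Step 3: effect of adjustment on variance.** In a simulation with 102 per arm and 40% versus 60%, a logistic model held three covariates, one of them prognostic, and gave a standardised risk difference. The half-width is 13.4 multiplied by the square root of the variance ratio.

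| Odds ratio per SD | Variance, adjusted/crude | 95% half-width (points) |
|---|---|---|
| 1.0 | 1.02 | 13.6 |
| 1.35 | 1.00 | 13.4 |
| 1.65 | 0.96 | 13.2 |
| 2.0 | 0.90 | 12.8 |
| 2.5 | 0.87 | 12.5 |

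**Step 4: effect on power.** A separate simulation used one combined prognostic score and 4,000 trials per setting, and compared the uncorrected chi-square with the Wald test from the adjusted logistic model.

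| Odds ratio per SD | 40% v 60%: crude, adjusted | 28% v 48%: crude, adjusted |
|---|---|---|
| 1.0 | 83.6%, 81.7% | 85.1%, 84.8% |
| 1.5 | 83.0%, 82.6% | 83.9%, 85.0% |
| 2.0 | 83.8%, 85.6% | 84.7%, 87.0% |
| 2.5 | 84.0%, 87.7% | 84.8%, 89.2% |

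The gain is nil, or slightly negative, when the score is weak. It is about 2 points at an odds ratio of 2.0 and about 4 points at 2.5. At 41.9% versus 61.9% and an odds ratio of 2.5, power goes from 83.7% to 88.4%, a gain of 4.7 points.

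**Step 5: chance imbalance.** Without stratification, the between-arm difference in a standardised covariate has SD √(2/102) = 0.14, and exceeds 1.96·0.14 = 0.27 SD in absolute value in 5% of randomisations. If the covariate explains 9% of the variance in abstinence (about an odds ratio of 2.0 per SD), one SD corresponds to √0.09·√(0.5·0.5) = 0.15, or 15 points. The crude difference then moves by about 0.15·0.14 = 2 points typically and 0.15·0.27 = 4 points at the 5% extreme, against a target of 20.

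**Step 6: which summary gains.** The marginal odds ratio at 40% versus 60% is (0.6/0.4)/(0.4/0.6) = 2.25. The conditional odds ratio is 2.45 when the covariate has an odds ratio of 2.0 per SD. Adjusting the logistic model alone therefore changes what is estimated, and it does not narrow the interval for the log odds ratio. The precision gain belongs to the standardised (marginal) measures.

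**The case against.** The strongest reply is that nothing here is wrong. Under randomisation the chi-square is a valid test, the crude estimate is unbiased over randomisations, and its interval already allows for chance imbalance. The stated method also matches the sample size calculation. All of this stands. A reader might infer that the main analysis is biased or confounded, and the protocol does not support that.

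A reader might also infer that the protocol names dependence and consumption as predictors of quitting. It does not. The Background says that smokers with depressive symptoms "present higher levels of cigarette consumption, greater nicotine dependence", and lists these features beside failed quit attempts. Only depressive symptoms are said to affect the outcome of cessation treatment, so the case must rest on them.

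Third, the size of the gain is assumed. The protocol says that symptoms can affect outcome but gives no strength, and at the weak end adjustment gains nothing. This stands too, and it limits how strongly the point can be put.

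Finally, multiple regression is listed, and an analysis plan that is not shown may name covariates. This rules out a claim that the baseline data go unused. It does not remove the point, because the article itself fixes the unadjusted comparison as the main analysis and lists regression separately.

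**Conclusion.** The point holds as a minor improvement in efficiency and robustness. The main BA-versus-standard abstinence comparison is unadjusted, while the one baseline factor that the protocol says affects quitting is measured before allocation and, on the stated text, not balanced by design.

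With 102 per arm, 40% versus 60%, and three covariates of which one is prognostic, the change in variance runs from about +2% to -13% over odds ratios per SD of 1.0 to 2.5. Power rises by zero to about 4 to 5 points. Where the covariate explains 9% of the variance, a typical chance imbalance moves the crude difference by about 2 points. The protocol does not say where in this range the trial lies, so a claim that substantial power is being lost would go too far.

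**What to change.** In Statistical analysis, make the main BA-versus-standard abstinence analysis at each visit a logistic regression on arm and continuous baseline BDI-II. Fix the model and covariate list before any comparison by arm. Recruitment is reported as ongoing, so at the time of the article this could still be done. Baseline dependence (FTCD or NDSS) and cigarettes per day may be added because they are already collected, but not on the ground that the protocol calls them predictors of quitting.

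Report the standardised (marginal) difference in quit proportion with its 95% CI. If an odds ratio is kept, report the marginal one with its 95% CI. Retain the crude chi-square and odds ratio as supportive analyses.

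The costs are slightly more programming, a change of headline measure from the odds ratio to a difference in proportions, and a negligible loss of precision (about 2% in variance) if the covariates prove not to be prognostic. No new data, visits or participants are needed.

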## Aims

The main aims of the present randomized controlled trial are: 1) to assess the efficacy (smoking abstinence rates) of a cognitive-behavioral smoking cessation treatment with elements from behavioral activation for managing depressed mood, compared with a standard smoking cessation treatment, at the end of treatment, and at 3-, 6-, and 12-month follow-ups; and 2) to assess whether the applied cognitive-behavioral smoking cessation treatment plus behavioral activation improves depressed mood, compared with a standard smoking cessation treatment, at the end of treatment and at 3-, 6-, and 12-month follow-ups.

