#### Treatment delayed control group

It will be a delayed-treatment control group for a period of 3 months. After the 3-month period, another assessment will be carried out, and then participants will be offered to participate in a smoking cessation treatment (Table 2).

**Table 2 Tab2:** Summary of session-by-session outline of intervention procedures

Ss	Cognitive-behavioral Smoking Cessation Treatment (CBSCT)	CBSCT + Behavioral Activation
1	Overview of treatment Smoking cessation treatment rationale Review self-monitoring (tracking cigarettes and smoking antecedents and consequences) Indications about how to graphically represent the No. of cigarettes/day Reasons for smoking and for quitting Discuss smoking history and quit experiences Explain and provide written materials about tobacco, nicotine dependence, smoking health consequences and quit smoking benefits Explain nicotine fading through brand change Physiological feedback (CO) As homework: - Brand change - Communicate to at least one person [family, friend, coworker, etc.) that he/she is trying to quit smoking in the next 30 days - Not smoke more cigarettes than the average of those smoked the previous week - Leave a third of the cigarette without smoking - Refuse cigarette offers	Overview of treatment Smoking cessation treatment rationale Review self-monitoring (tracking cigarettes and smoking antecedents and consequences) Indications about how to graphically represent the No. of cigarettes/day Reasons for smoking and for quitting Discuss smoking history and quit experiences Explain and provide written materials about tobacco, nicotine dependence, smoking health consequences and quit smoking benefits Explain nicotine fading through brand change Physiological feedback (CO) As homework: - Brand change - Communicate to at least one person (family, friend, coworker, etc.) that he/she is trying to quit smoking in the next 30 days - Not smoke more cigarettes than the average of those smoked the previous week - Leave a third of the cigarette without smoking - Refuse cigarette offers

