### Outcomes

#### Primary outcome measures

Point-prevalence abstinence defined according to Russell Standard (RS) criteria [56]. Participants will be considered abstinent if they report abstinence, not even a puff of a cigarette, for ≥24 h at the end of treatment, and for ≥7 days prior to follow-up day at the 3-month follow-up, and have an expired carbon monoxide reading of ≤10 ppm. At the 6- and 12-month follow-ups, participants will be considered abstinent if they report abstinence, not even a puff of a cigarette, for ≥30 days prior to follow-up day, and have an expired carbon monoxide reading of ≤10 ppm.Significant change in depressive symptoms on the Beck Depression Inventory-II (BDI-II) from baseline to the end of treatment, and at 3-, 6-, and 12-month follow-up.Significant change in depressive symptoms on the Hamilton Depression Rating Scale (HDRS) from baseline to the end of treatment, and at 3-, 6-, and 12-month follow-up.

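### For the depression co-primaries the named test compares the active arms with the delayed-treatment control, whereas Aim 2 compares behavioral activation with standard treatment

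*Protocol article*

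**What the plan says.** The Aims section of the protocol article sets the second main aim as whether the combined treatment "improves depressed mood, compared with a standard smoking cessation treatment, at the end of treatment and at 3-, 6-, and 12-month follow-ups". This is a two-arm contrast at four time points.

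Under Primary outcome measures, two of the three primaries are depression scales: "Significant change in depressive symptoms on the Beck Depression Inventory-II (BDI-II) from baseline to the end of treatment" and, in parallel wording, "Significant change in depressive symptoms on the Hamilton Depression Rating Scale (HDRS) from baseline to the end of treatment". Both definitions go on to the three follow-ups.

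The Statistical analysis section treats the two kinds of primary outcome differently. For abstinence it names active versus control at end of treatment and also a comparison "between BA intervention group and standard intervention group at the end of treatment, and at 3-, 6-, and 12-month follow-ups". For continuous outcomes it names a t-test to determine "whether there were any significant differences between the two active treatment groups and the control group in continuous variables such as BDI-II score". The paragraph closes: "We also will conduct mediation analysis, multiple regression analysis, repeated measures ANOVA, and survival analysis".

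Of the control arm the protocol says: "It will be a delayed-treatment control group for a period of 3 months". One more assessment follows, and then treatment is offered.

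**The concern.** The test named for mood has a different contrast from the aim it should serve. A comparison with a waiting list shows whether receiving a program helps mood. It does not show what BA adds to a program that both active arms receive. It also cannot reach 6 or 12 months, because no untreated control exists by then.

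Two features add to the problem. The HDRS is not named in the analysis section and enters only through the phrase about variables such as the BDI-II. The outcome definitions make statistical significance part of the endpoint and describe change over time, so they do not supply the missing between-arm quantity.

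At stake is which mood result counts as the trial's answer. With the contrast unassigned, a benefit over the waiting list could be presented as the primary mood finding, and the BA-versus-standard estimate would be left to a choice made after the data are seen.

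**Working it through.** **1. Aim, outcome and test side by side**

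| | Abstinence | BDI-II | HDRS |
|---|---|---|---|
| Contrast in the aim | BA v standard | BA v standard | BA v standard |
| Time points in the aim | end, 3, 6, 12 months | same | same |
| Contrast in the analysis section | active v control, and BA v standard | active v control | none by name |
| Time points in the analysis section | end (control); all four (BA v standard) | none given | none given |

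The depression columns lack the entry that the abstinence column has.

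**2. The plan's own sample size**

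The calculation is "To detect a 20% difference between the two active groups in the proportion of individuals with tobacco abstinence after treatment", with 80% power and a 0.05 level, giving 102 per active group. Taking 28% v 48% (28% is the low end of the stated range of quit rates), two-sided:

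- Pooled p = 0.38. n = [1.96·√(2·0.38·0.62) + 0.8416·√(0.28·0.72 + 0.48·0.52)]² / 0.20² = (1.3454 + 0.5653)² / 0.04 = 91.3, so 92.
- With continuity correction: (91.3/4)·[1 + √(1 + 4/(91.3·0.20))]² = 101.0, so 102.

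The stated 102 is reproduced. It concerns abstinence only; no effect size or SD is given for the BDI-II or HDRS.

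**3. What each contrast can detect**

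Detectable difference in SD units, two-sided 0.05, 80% power, normal approximation: (1.960 + 0.842)·√(1/n₁ + 1/n₂).

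- BA v standard, 102 v 102: 2.802 × 0.1400 = 0.392
- One active arm v control, 102 v 51: 2.802 × 0.1715 = 0.480
- Both active arms pooled v control, 204 v 51: 2.802 × 0.1566 = 0.439

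The contrast that answers Aim 2 is therefore also the best-supported of the three.

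**4. What baseline adjustment adds to BA v standard**

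Let r be the correlation between baseline and follow-up score. Relative to the SD of the follow-up score, the working SD is 1 for a follow-up-score t-test, √(2(1 − r)) for a change-score t-test, and √(1 − r²) for ANCOVA. The effect of 0.30 SD and the values of r are assumptions. Power is from the noncentral t distribution with 102 per arm:

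| r | t-test, follow-up score | t-test, change score | ANCOVA |
|---|---|---|---|
| 0.5 | 57% | 57% | 69% |
| 0.6 | 57% | 66% | 76% |
| 0.7 | 57% | 79% | 85% |

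At r = 0.7 the detectable effect (normal approximation) is 0.392 × 0.775 = 0.304 SD for change scores and 0.392 × 0.714 = 0.280 SD for ANCOVA.

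**The case against.** **The listed models may cover Aim 2.** Both scales are scheduled at baseline and four later visits (Table 1), so repeated measures ANOVA is a natural route to an arm-by-time comparison. The Aims section and the Discussion both show the intent to compare the active arms on mood. A reader might infer that the trial will never estimate what BA adds; the documents do not support that. What remains is that the ANOVA and the regression carry no outcome, contrast or time point, while the one test tied to the BDI-II carries a different contrast.

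**The t-test sentence may mean all pairs of the three groups.** This is possible, since a t-test takes two groups at a time. The preceding sentence counts against it, because there BA versus standard is spelled out separately from active versus control.

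**The unseen analysis plan may settle it.** Assigning models to endpoints is often left there. Here, though, the protocol states a contrast, and that contrast differs from its own aim.

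**Baseline.** A reader might infer that the t-test ignores baseline. The text does not say whether it uses follow-up or change scores, and the outcome definitions make change scores at least as natural. Either test is valid under randomization. This objection stands, and it shrinks the ANCOVA gain at r = 0.7 from 28 points (57% to 85%) to 6 (79% to 85%).

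**Significant change.** A reader might infer that each arm will be tested against its own baseline and the p-values compared. No such analysis is planned. The wording needs an edit, but no error rate follows from it.

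**Conclusion.** The concern holds for the contrast. For two of the three primary outcomes, the only explicitly assigned test is active versus delayed-treatment control. That cannot answer Aim 2 at any time point, and the control arm ends before 6 and 12 months. This rests on the text alone and needs no assumption.

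Baseline adjustment is secondary. It improves precision at no cost: with an assumed 0.30 SD effect, 102 per arm and r from 0.5 to 0.7, ANCOVA gains 12 to 28 points of power over a follow-up-score t-test and 6 to 12 points over a change-score t-test. Those figures depend on an effect and a correlation that the protocol does not give. No sample-size figure is shown to be wrong on this point.

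**What to change.** - In Statistical analysis, name the BA-minus-standard difference in mean BDI-II and in mean HDRS at end of treatment and at 3, 6 and 12 months, each with a 95% CI, as the Aim 2 analysis.
- Estimate it with a baseline-adjusted model: ANCOVA at each time point, or one mixed model with arm, time, arm-by-time and baseline score.
- Keep active versus control as a separately labeled contrast within the control's 3-month period.
- Say which outcomes the repeated measures ANOVA and the multiple regression serve, or drop them where the model above replaces them.
- In the Abstract and in Primary outcome measures, replace significant change with change in score.

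The cost is a few sentences. Both scales are already scheduled at every visit needed (Table 1), so no new data and no larger sample are required. As recruitment is ongoing, the change should be made and dated before outcome data are compared by arm.

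### Intention-to-treat is promised for every analysis, but the only missing-data rule covers tobacco variables, and the tests named for continuous outcomes do not by themselves keep participants with missing BDI-II or HDRS scores

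*Protocol article*

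**What the plan says.** The Statistical analysis section of the protocol article opens with a general commitment: "All data analysis will follow the intention-to-treat principle". It explains this as the "inclusion in the primary analysis of data from all the participants randomized to each group, including those who drop out of the study".

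The Primary outcome measures section lists three outcomes. The first is CO-verified point-prevalence abstinence. The other two are depression scales: "Significant change in depressive symptoms on the Beck Depression Inventory-II (BDI-II) from baseline to the end of treatment" and "Significant change in depressive symptoms on the Hamilton Depression Rating Scale (HDRS) from baseline to the end of treatment", each also assessed at 3, 6 and 12 months.

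The one missing-data rule is in the section on target population, blinding, randomization and procedure. Of participants who cannot be located it says that "they will be considered to be smokers, and at the same level (in terms of tobacco-related variables) as at the baseline assessment". The same section places the end-of-treatment assessment within the eighth treatment session.

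For continuous outcomes, the Statistical analysis section names t-tests of the active groups against the control group and gives the BDI-II score as an example. HDRS is not named and comes in only as another continuous variable. The section then adds: "We also will conduct mediation analysis, multiple regression analysis, repeated measures ANOVA, and survival analysis". None of the methods in that list is tied to an outcome.

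**The concern.** For abstinence, the promise and the method fit together: a participant who is lost counts as a smoker and stays in the denominator. For BDI-II and HDRS nothing plays that part. The promise covers all analyses, the rule stops at tobacco variables, and the tests named use only the scores that exist.

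This matters because of who is likely to be missing. The procedure section assumes that people who cannot be located are smoking. The Background links depressive symptoms with failed quit attempts and relapse, and links mood improvement with staying abstinent. On these premises, people without a score probably have worse mood than those with one. They would count as failures for abstinence and drop out of view for mood. With the end-of-treatment assessment held in session 8, those who have stopped attending are the likeliest to lack that score, although the article does not say that they will go unassessed.

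**Working it through.** **Inputs from the article.** 102 participants per active arm; a 20% difference in abstinence; power 80%; p-value 0.05; quit rates between 28% and 61.9%; BDI-II and HDRS measured at baseline and at four later time points (Table 1). The article gives no attrition rate and no standard deviation for either scale, so every attrition figure below is an assumption.

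**1. The plan's own figure.** Take 28% against 48% (the bottom of the stated range plus 20 points), two-sided, with continuity correction.

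- Uncorrected: n = [1.960·√(2·0.38·0.62) + 0.842·√(0.28·0.72 + 0.48·0.52)]² / 0.20² = (1.345 + 0.565)² / 0.04 ≈ 91.3, which rounds up to 92.
- Corrected: n = (91.3/4)·[1 + √(1 + 4/(91.3·0.20))]² ≈ 101.02, which rounds up to 102.

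The stated 102 is reproduced. It rests on abstinence alone and makes no statement about the depression scales.

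**2. The promise against the methods.**

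| Primary outcome | Rule for missing values | Method stated | Are dropouts kept? |
|---|---|---|---|
| Abstinence | Counted as smoker | Chi-square, odds ratio | Yes |
| BDI-II | None stated | t-test (named) | Only if scores are filled in first |
| HDRS | None stated | t-test (by extension from BDI-II) | Only if scores are filled in first |

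Repeated measures ANOVA is not assigned to any of these. It is the listed method that would most naturally serve the second aim, which compares the active arms on mood at four time points. In its classical form it needs a score at every occasion.

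**3. How many would be left (illustration).** Let m be the proportion missing at each visit. A t-test at one visit keeps 102·(1 − m). With missingness independent between visits, a four-visit complete-case analysis keeps 102·(1 − m)⁴.

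| m | One visit | All four visits |
|---|---|---|
| 5% | 102·0.95 ≈ 97 | 102·0.815 ≈ 83 |
| 10% | 102·0.90 ≈ 92 | 102·0.656 ≈ 67 |
| 15% | 102·0.85 ≈ 87 | 102·0.522 ≈ 53 |
| 20% | 102·0.80 ≈ 82 | 102·0.410 ≈ 42 |

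Independence leans toward a large loss. People who leave tend to stay away, and if the same 10% missed every visit, 92 rather than 67 would be complete.

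**4. Precision.** For a two-arm contrast at one visit without baseline adjustment, the difference detectable with 80% power is (1.960 + 0.842)·√(2/n) standard deviations: 0.39 at n = 102, 0.41 at 92, 0.44 at 82 and 0.48 at 67.

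**5. Bias (illustration).** Suppose there is no true effect, and the participants highest on a latent tendency to leave, correlated 0.5 with the mood score, are missing. The mean of those kept is −0.5·φ(z)/(1 − r), where r is the proportion missing and z the cut-off.

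- r = 30%: −0.5·0.348/0.70 = −0.248.
- r = 15%: −0.5·0.233/0.85 = −0.137.

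The arm with more dropout looks better by about 0.11 SD. With 20% missing in both arms by the same mechanism, the between-arm difference is unbiased. Bias in the contrast therefore needs dropout that differs between arms in amount or in kind.

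**The case against.** The strongest reply is that nothing in the article says incomplete cases will be deleted. The text says the opposite, and a t-test or ANOVA run on imputed scores would keep everyone. A reader might infer that the BDI-II and HDRS analyses will be completer analyses that contradict the intention-to-treat sentence. The document does not support that, because it rests on how standard software treats missing values and not on a stated plan. Even without imputation, a t-test at one visit leaves out only those without a score at that visit, which is an available-case analysis and not a completer analysis.

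It is also true that repeated measures ANOVA is not attached to either scale, that HDRS is reached only through the BDI-II example, and that imputation detail may sit in a full protocol or analysis plan that is not shown. Its absence from an article would be no fault.

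All of this limits the point without removing it. The article does more than stay silent: it extends its promise to all analyses, confines its one rule to tobacco variables, and names methods for continuous outcomes that cannot meet the promise on their own. A better method is available at little cost.

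**Conclusion.** The mismatch is real and affects two of the three primary outcomes; the abstinence analysis is untouched. As written, the t-test (and ANOVA, if it is used for these scales) would not deliver intention-to-treat for BDI-II and HDRS unless missing scores are handled first. That is as far as the text goes. It does not establish that participants will be deleted.

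The size cannot be derived from the article. At an assumed 10% missing per visit, about 92 of 102 per arm remain for a single-visit test, and between about 67 (independent missingness) and 92 (the same people always missing) for an analysis needing all four visits. That participants without scores are not a random subset follows from the article's own premises about dropout, relapse and mood; how far the treatment contrast would be biased remains unknown. The plan should be changed on this point. Confidence is high in the mismatch and moderate at most in its consequences.

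**What to change.** Analyse BDI-II and HDRS with a likelihood-based mixed model for repeated measures: arm, visit, arm-by-visit interaction and unstructured covariance, with the baseline score modelled as part of the outcome vector. With baseline only as a covariate, a participant with no later score would contribute nothing; with baseline in the outcome vector, every randomised participant with a baseline score enters. Multiple imputation is an acceptable alternative. Report the contrast of behavioral activation against standard treatment at each visit, which is what the second aim asks for.

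Both approaches assume that the observed scores explain the missingness. Add one sensitivity analysis that shifts dropouts' imputed scores toward worse mood, to show how far the conclusion depends on that.

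The cost is a change of wording and modest extra analysis work. The same model could be extended to EROS and BADS, and end-of-treatment questionnaires could be sought at week 8 from participants who have stopped attending, since recruitment was still under way. Both are optional and the point does not depend on them.
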